**Figure 1 F1:**
[figure not shown]
Study protocol.

### Interventions

2.2

The facial candling treatment will be conducted for 15 minutes by a certified practitioner using a plain unscented facial candle. The facial candle is made of cloths which are soaked in beeswax. The facial candle is 9 to 10 inches in length and 0.25 to 0.5 inches in diameter. First, the patients will lie down on a massage table bed. Then, their both eyes will be closed with cotton to prevent the ash of the candle irritated the eyes during the treatment. Next, the candle will be kept in a vertically upright position and the large end of the candle is lit. After that, smoke that released by the candle will be passed around the patients face. Last, the face will be cleansed with water. Meanwhile, the control group will lie in a relaxation positions within 15 minutes prior assessment (no facial candling treatment) (Fig. 1).

### Blood and mucus collection

2.3

Before and after the facial candling treatment, about 10 mL of venous blood will be taken by a certified phlebotomist. The whole blood will be collected into plain polyethylene tube until blood clot formation. After that, clots are separated from the wall of tube using a wooden applicator stick. Approximately 3 mL of nasal mucus will be collected with a suction from an aided vacuum that does not require chemical stimulation to prevent the introduction foreign substances into the nasal fluids. A small rubber-tipped vacuum device will be inserted gently inside the nasal passageways to stimulate nasal secretions. Both blood and nasal mucus samples will be collected and centrifuged (10,000 g and 4 °C for 15 minutes) to eliminate debris and cellular matter. The supernatant will be stored at −80 °C until analysis.

### Outcome measures

2.4

The primary outcome measure for this study is the difference in the level of SP in blood and nasal mucus samples in pre- and postintervention. The secondary outcome measures include the levels of inflammatory mediators (tumor necrosis factor alpha [TNF-α], IL-3, IL-5, IL-6, IL-10, and IL-13) in both blood and nasal mucus samples. Other secondary outcome measures also include the visual analogous scale (VAS) score (indicating the pain intensity) and the Rhinitis Quality of Life Questionnaire (RQLQ).

### Instruments

2.5

All samples will be analyzed individually using commercial human enzyme-linked immunosorbent assay kits (Table 1). The VAS is a measurement of pain and symptom intensity and has been found to be acceptable to patients and valid.^[25,26]^ The scale ranges is from “0” to “10” with a different facial expression whereby 0 represents “no pain/symptom” and 10 represents the “worst possible pain/symptom.” In this study, patients will be asked to rate their pain and symptom severity using the VAS pre- and postintervention. RQLQ will also be used to assess the disease-associated problems of the participants in 7 aspects of daily life: activities, sleep, nonnose/eye symptoms, practical problems, nasal symptoms, nose symptoms, and emotional symptoms. The score of each of the item is graded into 0 to 6. The total score of the 7 items will be calculated for every participant at baseline (1 day before) and 1 day after the intervention.

**Table 1 T1:**
[figure not shown]
Analytical and assessment characteristics.

### Sample size calculation

2.6

The sample size is calculated using Power and Sample Size software 3.1.2 version. The difference between the mean values of the intervention and control groups, and the standard deviation (postmassage) of SP levels^[27]^ will be used as parameters for sample size calculation given there is no previous finding of the immediate effect of facial candling treatment on SP. The mean levels of SP in the intervention group and control group are 50.43 and 56.27 pg/mL, respectively (the difference in the mean values between the experimental and control groups is 5.84 pg/mL).^[27]^ The type I error probability associated with this test of the null hypothesis is 0.05. A sample of 33 experimental subjects and 33 control subjects is therefore required to reject the null hypothesis that the population means of the experimental and control groups are equal, with a probability (power) of 0.8.

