### Study design and patient recruitment

2.1

A randomized, nonblinded, controlled trial will be carried out at a health clinic located at Universiti Teknologi MARA (UiTM), Puncak Alam, Malaysia. A total of 66 allergic rhinitis patients who have seen ear–nose–throat specialist at a university health clinic and fulfill the inclusion criteria will be invited to participate in this study. Skin prick and puncture test (SPT) was performed to confirm the diagnosis before enrolment confirmation by otolaryngologists to exclude patients with sinusitis and nasal polyps.

An otorhinolaryngology specialist will conduct confirmatory medical examination for the subjects and screening based on inclusion and exclusion criteria. The inclusion criteria are as follow: has a positive skin prick test, age between 18 and 65 years old, and negative urine pregnancy test for female. The participants will be excluded if they are diagnosed with chronic obstructive pulmonary disease, sinusitis/rhinosinusitis, nasal polyps, asthma, taking medication containing analgesic, antihistamine and steroid, and pregnant.

An explanatory statement will be given and writing informed consent will be obtained prior to the commencement of the study. The participant will then be randomly assigned into 2 groups: allergic rhinitis patients or control groups (Fig. 1). Patients will be asked to choose among the sequentially numbered, sealed envelopes containing the group allocation, which will be determined by a computer-generated random number. An independent researcher produces the random numbers and prepares the envelopes. The current study is funded by UiTM and Ministry of Higher Education of Malaysia. Ethical approval has been obtained from the UiTM Research Ethics Committee (REC/113/115). The trial is registered under Australia New Zealand Clinical Trial Registry (ACTRN12616000299404).

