## Discussion

3

There is growing awareness that the knowledge of SP may help to develop new methods to treat pain and inflammation.^[19,28,29]^ For example, SP and inflammatory mediators appear to play a role in allergic rhinitis.^[30,31]^ Recently, the role of SP in the pathophysiology of clinical syndromes such as inflammatory rhinitis and diseases with chronic inflammatory pain in general is becoming clearer.^[32]^ It can be expected that the development of drugs and interventions aimed at the modulation of SP will be able to help in treatment of pain associated with these diseases. Previous study used the level of SP in nasal mucus to indicate the severity of pain in many chronic pain conditions, because the amount of SP is significantly greater in nose mucus than in plasma.^[33]^

As there is no previous finding related to facial candling, we explored studies that trialed effectiveness of other complimentary treatment methods. For example, 23 patients (19 were serologically tested positive for allergic diseases) with persistent allergic rhinitis were treated with 4 acupoint herbal plaster applied using the moxibustion technique. Clinical outcomes measured using the RQLQ indicated that the patients tested positively for allergic disease responded better to the treatment. Furthermore, IL-13 immune response was downregulated in that particular group of patients.^[22]^ Similarly, another study demonstrated the effectiveness of subcutaneous injectable immunotherapy in treating the sinus inflammation and pain in 281 allergic rhinitis patients. The subcutaneous immunotherapy as treatment of allergic rhinitis led to a reduction in all symptoms studied, improving the QoL of patients.^[34]^ Antiinflammatory effects of acupuncture and their relevance to allergic rhinitis have also been examined.^[35]^ Acupuncture has been shown to significantly reduce histamine-induced symptoms of allergic rhinitis. Furthermore, the study showed that there is significantly reduce of IL-4 and IL-10 in allergic rhinitis patients as acupuncture treatment has been applied^[36]^ and their finding was supported by Petti et al,^[37]^ who revealed the significant decrease of IL-10 immediately after acupuncture treatment. Interestingly, they showed unpredicted significant decrease of IL-2 and no significant changed in IL-6.

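### The 80% power in section 2.6 belongs to a single comparison of SP means, not to the primary outcome, which is the pre-to-post change in SP in two fluids

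*Protocol article*

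**What the plan says.** Section 2.6 of the protocol article takes its inputs from one cited study, because no earlier data exist on facial candling and SP. It gives the means ("The mean levels of SP in the intervention group and control group are 50.43 and 56.27 pg/mL, respectively"), notes that "the difference in the mean values between the experimental and control groups is 5.84 pg/mL", and names as the measure of spread "the standard deviation (postmassage) of SP levels", without printing its value. The error rate is given as "The type I error probability associated with this test of the null hypothesis is 0.05", and 33 patients per arm are said to be enough to reject equality of the two population means "with a probability (power) of 0.8". The calculation names no fluid.

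Section 2.4 defines the primary outcome as "the difference in the level of SP in blood and nasal mucus samples in pre- and postintervention". The abstract likewise makes it the change in SP in both fluids, compared between the groups. Section 2.7 applies a paired t test, or a Mann–Whitney test if the data are skewed, to pre/post differences within and between groups, at P below 0.05.

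**The concern.** A power statement holds for one endpoint, one measure of spread and one test. Here the calculation uses the spread of a post-treatment level, while the outcome is a change from baseline. The two spreads differ unless the pre/post correlation happens to be 0.5. The calculation also describes one SP variable, while the trial has two primary ones.

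What is at stake is how the result will be read. If SP shows no significant difference in blood or in mucus, readers will judge that against an 80% chance of detection that was not calculated for the test performed.

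**Working it through.** **Inputs from the document.** Section 2.6: means 50.43 and 56.27 pg/mL, alpha 0.05, power 0.80, 33 per arm. Sections 2.4 and 2.7 and the abstract: the outcome is change, in two fluids.

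**Assumptions, not in the document.** The test is two-sided, the between-group comparison is a two-sample t test, the SD is the same before and after, and the pre/post correlation r is varied over a range. That the two means are post-treatment values, and that the source is a massage study, is inferred from the label attached to the SD.

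**Step 1: the plan's own figure.** 56.27 − 50.43 = 5.84 pg/mL, as stated. Because the SD is not printed, 33 per arm cannot be reproduced independently and can only be solved backwards. With the noncentral t distribution, 33 per arm and 80% power, the SD is 8.34 pg/mL, so d = 5.84 / 8.34 = 0.70. (SDs from about 8.21 to 8.34 all round up to 33 per arm. The normal approximation gives 8.47 two-sided and 9.54 one-sided.) The sample size is thus consistent with one two-sample t test at d = 0.70.

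**Step 2: the same inputs applied to change.** Under randomisation the expected group difference in change equals the expected group difference in post-treatment means, so 5.84 carries over. Only the spread differs:

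SD of change = SD × √(2(1 − r))

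| Assumed r | √(2(1 − r)) | SD of change (pg/mL) | Power, 33 per arm |
|---|---|---|---|
| 0 | 1.414 | 11.79 | 51% |
| 0.3 | 1.183 | 9.87 | 66% |
| 0.5 | 1.000 | 8.34 | 80% |
| 0.7 | 0.775 | 6.46 | 95% |
| 0.8 | 0.632 | 5.27 | 99% |

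The stated 80% is recovered only at r = 0.5.

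**Step 3: two fluids.** The article does not say whether success needs both fluids. If it does, and each has 80% power, the joint power is at least 0.80 + 0.80 − 1 = 0.60, at most 0.80, and 0.80 × 0.80 = 0.64 if the two results are independent.

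**Step 4: a baseline-adjusted comparison.** In an analysis of covariance (ANCOVA) of post-treatment SP on group and baseline SP, the residual SD is approximately SD × √(1 − r²), which never exceeds the post-treatment SD. With the same d and n, power is about 80%, 84%, 90%, 97.5% and 99.7% at r = 0, 0.3, 0.5, 0.7 and 0.8. This ignores the degree of freedom spent on the covariate and any chance baseline imbalance, so at r near 0 the true figure is slightly under 80%. Hence the wording: about 80% or more.

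**The case against.** The strongest reply is that nothing is miscalculated. The subtraction is right, 33 per arm fits a coherent set of inputs, and the article explains why it borrowed from a surrogate study. The SD of 8.34 is itself solved from the sample size, so it cannot count as evidence against that sample size. The direction is also open. Samples are taken before and after one 15-minute session, a setting in which a high correlation is at least as plausible as a low one, and above r = 0.5 the change test has more than 80% power. All of this stands. A reader might infer that the trial is underpowered, but the document gives no correlation and no SD of change, so it does not support that.

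A reader might also infer lower power in mucus from the Discussion's statement that "the amount of SP is significantly greater in nose mucus than in plasma". That sentence concerns levels and says nothing about spread or treatment differences. If both scale with the level, d stays at 0.70 and power stays at 80%. No mucus SD is given, so no power figure for mucus can be derived.

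The unprinted SD and the absence of a dropout margin are details that an article commonly leaves to the full protocol, and they are not counted here as errors.

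What the reply leaves untouched is the mismatch: the article prints both a power and a primary outcome, and the first was not computed for the second.

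**Conclusion.** The point holds in limited form. The power of 0.8 in section 2.6 applies to one between-group comparison of SP means with a post-treatment SD. It does not describe the primary test of change in two fluids. On the plan's implied d of 0.70, power for change runs from 51% to 99% as the assumed correlation goes from 0 to 0.8. If both fluids were required and each had 80%, joint power would be 60% to 80%. These figures rest on a back-solved SD, a two-sided t test, equal SDs before and after, complete data and assumed correlations. They show that the power is undetermined, not that it is too low, and they show no error in 33 per arm. The fault is worth correcting because the remedy needs no further patients or samples.

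**What to change.** Keep 66 patients and amend two sections together. Changing 2.6 alone would again describe the power of a test that is not planned.

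- **Section 2.7:** make the primary between-group analysis an ANCOVA of post-intervention SP adjusted for baseline SP, separately for blood and for nasal mucus.
- **Section 2.6:** state that, for each fluid and with complete data, 33 per arm gives about 80% power or more to detect a difference of 0.70 SD in post-intervention SP, which is 5.84 pg/mL if the SD is about 8.34 pg/mL. Replace the back-solved SD with the value actually used, and say which fluid the surrogate figures refer to.

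The cost is small. Baseline and post-intervention samples are already planned in both fluids. The power claim becomes narrower, because it is made per fluid and in SD units where no fluid-specific figures exist. The provision in 2.7 for skewed data would need to be reworded to fit the ANCOVA.

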### Data analysis plan

2.7

Data will be analyzed using SPSS software version 20.0. Mean, standard deviation, and range will be calculated for each variable. Data will be tested for normality; paired *t* test will be used (if the distribution is normal) or Mann–Whitney (if the distribution is skewed) to measure the differences pre- and postintervention within and between groups for every outcome measure. A *P* value of less than 0.05 will be used to show that the result is statistically significant.

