**Method and analysis::**

A randomized, nonblinded, controlled trial will be carried out by recruiting a total of 66 eligible allergic rhinitis patients who fulfill the inclusion criteria from a university health center. The subjects will be randomly assigned into 2 groups: intervention group receiving facial candling treatment and control group (no treatment given). Samples of blood and nasal mucus will be collected right before and after intervention. Samples collected will be analyzed. The primary outcomes are the changes in the level of SP in both blood and mucus samples between both groups. The secondary outcomes include the levels of inflammatory mediators (ie, tumor necrosis factor alpha, interleukin (IL)-3, IL-5, IL-6, IL-10, and IL-13) and the severity of allergic rhinitis symptoms as measured by a visual analogous scale and QoL using the Rhinitis Quality of Life Questionnaire (RQLQ).

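### Section 2.7 lets a normality test choose between a within-arm and a between-arm test, so with normal data the named test cannot address the comparison the trial is sized for

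*Protocol article*

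**What the plan says.** Section 2.7 of the protocol article gives the selection rule: "Data will be tested for normality; paired *t* test will be used (if the distribution is normal) or Mann–Whitney (if the distribution is skewed"). Its scope is "to measure the differences pre- and postintervention within and between groups for every outcome measure". No other test is named, and the section does not say whether levels or changes are checked for normality.

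The comparison that matters is given elsewhere. The abstract states: "The primary outcomes are the changes in the level of SP in both blood and mucus samples between both groups". Section 2.6 sizes the trial to "reject the null hypothesis that the population means of the experimental and control groups are equal". Section 2.4 words the primary outcome more loosely, as the "difference in the level of SP in blood and nasal mucus samples in pre- and postintervention", without naming the arms.

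**The concern.** A selection rule of this kind normally offers two tests of the same comparison, one parametric and one rank-based. Here the parametric option is a within-arm test and the rank option is a between-arm test. A histogram-level property of the data would then decide whether the trial asks if SP changed after candling or if it changed more than in controls. Only the second question uses the randomisation.

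Both arms are sampled twice by venepuncture and nasal suction, and both spend about 15 minutes lying down (2.2, 2.3). Any effect of rest or repeat sampling on SP would appear in both arms, and a paired test in the candling arm would count it as a treatment effect. Because the rule runs outcome by outcome, blood SP and nasal SP, both primary, could also be judged under different hypotheses in the same report.

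**Working it through.** **1. What each branch can test**

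| Branch | Named test | Compares | Tests the 2.6 null? |
|---|---|---|---|
| Normal | paired t | pre vs post in one arm | No |
| Skewed | Mann–Whitney | two independent groups | Between-arm, but on ranks rather than means |

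The mismatch runs both ways. The normal branch has no between-arm test, and the skewed branch has no valid within-arm test, because Mann–Whitney ignores the pre/post pairing.

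**2. The plan's own figure**

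Inputs from 2.6: means 50.43 and 56.27 pg/mL, difference 5.84, alpha 0.05 (two-sided assumed), power 0.8, 33 per arm. The SD is not printed, so 33 cannot be reproduced directly. Solving for the SD:

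SD = 5.84 × √(33/2) / (1.960 + 0.842) = 8.47 pg/mL (8.34 with the t distribution).

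The CV is 8.34/56.27 ≈ 0.15. The figure of 33 per arm is therefore consistent with a two-sided test of two independent means, which confirms that the design comparison is between arms.

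**3. Cost of following the normal branch literally**

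Assume no treatment effect, normal changes, and a shift common to both arms of δ SDs of the change. For the candling arm's paired t test with n = 33, the noncentrality is δ√33, with 32 degrees of freedom and critical value 2.037.

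| δ | δ√33 | Paired t significant, candling arm | Significant in candling arm only | Between-arm t |
|---|---|---|---|---|
| 0 | 0 | 5% | 5% | 5% |
| 0.2 | 1.15 | 20% | 16% | 5% |
| 0.3 | 1.72 | 39% | 24% | 5% |
| 0.5 | 2.87 | 80% | 16% | 5% |

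The fourth column is p(1 − p), for example 0.387 × 0.613 = 0.237. It covers the habit of reading significance in one arm and not in the other as a treatment effect. Simulation of 20,000 trials gave 20%, 39% and 80% for the third column and 5% throughout for the last.

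**4. If both branches were between-arm tests**

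Suppose the paired t test is replaced by an independent-groups t test on change, which is not what 2.7 says. Choosing between it and Mann–Whitney by a Shapiro–Wilk test then kept type I error at 4.8% (CV 0.5) and 5.7% (CV 1.0). The harm is the change of hypothesis; the preliminary test does not in itself raise the error rate.

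**5. Whether a log scale helps**

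Power at 33 per arm of the step 4 switch on raw change, against a t test on log(post/pre). CVs other than 0.15 are assumptions.

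| CV | Proportional effect, lognormal levels, correlation 0.5: switch vs log | Additive 5.84 pg/mL, change SD 8.34: switch vs log |
|---|---|---|
| 0.15 | 77% vs 80% | 80% vs 78% |
| 0.5 | 66% vs 79% | 81% vs 63% |
| 1.0 | 60% vs 79% | 79% vs 44% |

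Across repeat runs and correlations of 0.5 and 0.7, the proportional gain is about 2 to 3 points at CV 0.15 and about 11 to 20 at CV 0.5 to 1.0. Under the additive effect, the log ratio loses about 2 points at CV 0.15, about 18 at CV 0.5 and about 35 at CV 1.0.

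**The case against.** The strongest defence is that 2.7 is compressed. The authors may mean paired t or its rank counterpart within arms, and independent t or Mann–Whitney between arms. On that reading the rule is fixed in advance, and step 4 shows its error rate is sound. A journal article may also leave details such as transformations to a fuller plan.

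The last point stands for transformations and summary statistics, but not for the test itself. The article names two tests and the rule for choosing between them, and the pair as named does not work. The charitable reading needs two tests that the text does not mention. Even then, the choice would still move between means and ranks by outcome, while section 2.6 fixes a null about means.

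A reader might go further and infer that the assays are analysed as raw pg/mL changes, that they are skewed, and that a log scale would recover some 12 to 20 points of power. The documents do not support this. Section 2.7 names no scale, no SP or mediator distribution is given, and the gain needs both an assumed CV of roughly 0.5 to 1.0 and a proportional effect. Section 2.6 states the effect as a difference of 5.84 pg/mL; with an additive effect the log ratio loses power.

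**Conclusion.** Wrong as written. The two tests offered as alternatives answer different questions, and with normal data the named test does not address the null that section 2.6 powers or the abstract's primary comparison. This follows from the text and needs no distributional assumption.

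The size does rest on assumptions. The 39% and 80% require a common shift of 0.3 or 0.5 SD of the change, normal changes, and a claim based on the candling arm's paired test. The documents give no estimate of such a shift, and without one the paired test stays at 5%. These figures show how exposed the rule is; they do not forecast this trial's error rate. The effect of a log scale on power is unsettled in sign as well as size.

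**What to change.** In 2.7, delete the normality test as the selector. For each outcome, name one between-arm analysis in advance: an independent-groups t-based comparison of the pre-to-post change, reported as a mean difference with 95% CI. Keep Mann–Whitney on the same change as a sensitivity analysis only, and label within-arm paired tests as descriptive. Align the wording of the primary outcome in 2.4 with the abstract.

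If a log scale is wanted for SP and the mediators, decide before the data are seen, state the effect as a ratio (50.43/56.27 = 0.90 for SP), and fix how values below the assay limit are handled. It should not be extended automatically to the VAS or RQLQ, which can be zero.

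The cost is wording: no extra patients, samples or visits. One consequence should be checked. Section 2.6 uses an SD of post-treatment levels, whereas the SD of a change is SD × √(2(1 − ρ)) when pre and post SDs are equal. The two agree at ρ = 0.5; power for change is above 0.8 if the pre/post correlation is higher and below 0.8 if it is lower.

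### Section 2.7 lets normality alone choose the test, so a paired t test falls on two unmatched arms and Mann–Whitney on paired pre/post data

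*Protocol article*

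**What the plan says.** Section 2.7 (Data analysis plan) gives one rule for choosing a test: "paired *t* test will be used (if the distribution is normal) or Mann–Whitney (if the distribution is skewed"). The same sentence states its scope: "to measure the differences pre- and postintervention within and between groups for every outcome measure". No other test is named. Only the shape of the distribution selects the test; the kind of comparison plays no part.

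The design sets what each comparison needs:

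- Section 2.1: "The participant will then be randomly assigned into 2 groups". No matching is described, so the arms are independent samples.
- Section 2.3: "Before and after the facial candling treatment, about 10 mL of venous blood will be taken". Each patient contributes two linked values.
- Abstract, Method and analysis: "The primary outcomes are the changes in the level of SP in both blood and mucus samples between both groups". The primary comparison is between arms.
- Section 2.4 words the primary outcome as "the difference in the level of SP in blood and nasal mucus samples in pre- and postintervention", without mentioning the between-arm contrast.
- Section 2.6 sizes the trial to "reject the null hypothesis that the population means of the experimental and control groups are equal", which is an independent two-group hypothesis.

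**The concern.** A paired t test needs a natural partner for each observation. Within an arm, a patient's pre value is the partner of the post value. Between arms there is no partner, so the software would pair unrelated patients by their position in the data file. Mann–Whitney needs two independent samples. That suits the two arms, but not the pre and post values of the same patients.

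The primary question is exposed in the normal branch. There the only named test that can properly be run is the pre/post test within each arm, and the wording of section 2.4 could steer an analyst to it. Separate within-arm tests do not estimate the randomised contrast, and they leave out whatever the control group's 15-minute rest does to SP. Alternatively, the analyst picks an unnamed test after seeing the data.

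**Working it through.** **1. The rule set against the design**

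| Data | Comparison | Test under section 2.7 | Suitable? |
|---|---|---|---|
| Normal | Within an arm, pre/post (paired) | Paired t | Yes |
| Normal | Between arms (independent) | Paired t | No |
| Skewed | Within an arm, pre/post (paired) | Mann–Whitney | No |
| Skewed | Between arms (independent) | Mann–Whitney | Yes |

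**2. The plan's own figure.** Section 2.6 gives means of 50.43 and 56.27 pg/mL, so the difference is 56.27 − 50.43 = 5.84, as stated ("the difference in the mean values between the experimental and control groups is 5.84 pg/mL"). It also gives alpha 0.05, power 0.8 and 33 per arm. The value of the SD and the sidedness are not printed, so 33 cannot be derived forward. Solving backwards for an independent two-sample t test, two-sided, the standardised difference is d = 0.700, and the SD is 5.84 / 0.700 = 8.34 pg/mL. (A one-sided test would imply an SD of about 9.44.) The figure of 33 per arm is thus consistent with an independent-samples test, which the normal branch of section 2.7 does not name.

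**3. Paired t across arms, normal data, 33 per arm** (simulation, 20,000 trials):

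- No true difference: type I error is about 4.9% for the paired test in arbitrary order and about 4.9% for the independent test.
- Difference 5.84, SD 8.33: power is about 78.3% (paired, arbitrary order) against 79.5% (independent), a loss of about 1 point.
- At d = 0.70, two arbitrary orders of the same data disagree on significance in about 6% of trials (5.5% to 6% across separate runs).
- Borderline illustration: one dataset with an independent-samples P of 0.050 gives paired P values from about 0.019 to 0.095 over the central 95% of row orders, and is significant in 42% of orders. This is close to the worst case, because the P value sits on the threshold.

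**4. Mann–Whitney on pre/post values within one arm of 33, no true change** (simulation, nominal 5%):

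| Assumed pre/post correlation | Mann–Whitney | Wilcoxon signed-rank |
|---|---|---|
| 0.3 | about 2% | 4.6% |
| 0.5 | about 0.9% | 4.8% |
| 0.7 | about 0.1% | 5.4% |

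The values were generated as normal. Mann–Whitney uses only ranks, so a common monotone transformation of pre and post values to a skewed scale leaves its column unchanged. Power falls as well: for an assumed 3 pg/mL shift at correlation 0.5 it is about 23% with Mann–Whitney and 50% with signed-rank.

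**5. What a correction based on change scores does to power.** Section 2.6 takes its SD from post-treatment values. If pre and post SDs are equal, the SD of a change is SD × √(2(1 − ρ)), so the standardised difference becomes 0.700 / √(2(1 − ρ)):

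- ρ = 0.3: 0.700 / √1.4 = 0.592, power about 66%
- ρ = 0.5: 0.700 / √1.0 = 0.700, power 80%
- ρ = 0.7: 0.700 / √0.6 = 0.904, power about 95%

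**The case against.** The strongest defence is that the authors meant the paired t test for comparisons within arms and Mann–Whitney for comparisons between them. The text does not say so: it ties the choice explicitly to normality. That reading would also leave normal between-arm data and skewed within-arm data without an assigned test. Nor is this a detail left to a separate analysis plan, because the article states the rule and states it wrongly.

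The objections about consequence do stand:

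- A reader might infer that every reported P value is unreliable. Two of the four combinations are correctly served. In particular, if SP is skewed, the primary between-arm comparison has a suitable test.
- A reader might also infer that the cross-arm paired t test produces false positives or a badly underpowered trial. It does neither, as step 3 shows. Its fault is a result that depends on file order and cannot be reproduced without knowing that order.
- The loss of patients from a paired test on unequal arms is conditional. The plan is for 33 and 33, and no imbalance is reported.
- Section 2.6 never states that SP is normal, so it is not known which branch will apply.
- The within-arm fault is conservative and would not create false claims of benefit. By itself it would be a minor matter.

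**Conclusion.** The point holds for two of the four combinations. The one that matters most is normal data between arms, where the plan names no suitable test for the comparison that the abstract calls primary and section 2.6 is sized for. The practical size is modest: type I error stays near 5% and about 1 point of power is lost, but the significance verdict turns on row order in about 6% of trials, mostly those with P near 0.05. If the arms end unequal, patients must also be dropped. The second mismatch, skewed data within an arm, makes the test too conservative, increasingly so as the pre/post correlation rises.

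The mismatch itself can be read directly from the text and rests on no assumption. The sizes rest on d = 0.70, back-solved for a two-sided test because the SD is not printed, and on assumed pre/post correlations, for which the protocol gives no value. The correction is still needed before analysis, because it concerns the primary test and otherwise leaves that choice open once the data are seen.

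**What to change.** Rewrite the rule in section 2.7 so that each test matches its comparison:

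- **Between arms (primary):** form each patient's pre-to-post change and compare the arms with an independent two-sample t test, or with Mann–Whitney on those changes if they are skewed.
- **Within arms (descriptive only):** use a paired t test, or the Wilcoxon signed-rank test if the changes are skewed.

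The paired t test should no longer appear as a between-group test. Whether the two-sample t test is pooled or Welch is a secondary choice and not part of this correction.

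The cost is about two sentences, with no new patients, visits or samples. There is one downside to record. Because section 2.6 uses a post-treatment SD, the change-score comparison keeps the stated 80% power only if the pre/post correlation of SP is about 0.5 or higher. The revised text should state the correlation it assumes.
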